### Randomisation

A random number generator embedded in the computer-assisted telephone interview (CATI) software will be used to allocate study participants to either receive the intervention or standard care after all baseline questions have been answered. Individuals will be randomised at a ratio of 1:1 in permuted blocks of randomly varying size (e.g. four and six), stratified by state (New South Wales, Queensland, Western Australia, Victoria/Tasmania), and type of stroke (ischaemic, haemorrhagic, TIA, other). The statistician will be blinded to the treatment group.

### Recruitment and screening

AuSCR or HSRVR will screen individuals for eligibility criteria and will send out invitation packs on behalf of the trial research team to potentially eligible database registrants (i.e. individuals 6 to 36 months post first stoke, aged 18 years and older). Invitation packs will include a cover letter from AuSCR or HSRVR, a participant information statement describing the project Additional file 2 (Model participant information statement), and two consent forms (one for study participation Additional file 3 (Model participant consent form) and one to allow the researchers to access the individual’s health care data (Medicare and Pharmaceutical Benefits Schemes; MBS and PBS) from the national registry). Participants will be asked to sign and return the consent forms in a replied, paid envelope to the research team. Due to potential physical limitations in the population being studied, carers will be able to consent on behalf of individuals by signing the consent form and indicating that they are a carer. Upon receipt of the signed consent forms, potential participants will be telephoned by the research team (enrolment call) to be screened regarding Internet and email access, and disability using the brief nine-item modified Rankin Scale. Potential participants will be, given an opportunity to ask questions about the study. Upon eligibility confirmation, participants will complete a baseline CATI after which they will be randomised.

Figure 1 outlines study recruitment and follow-up, while Fig. 2 contains an assessment schedule for the trial. To promote adherence to programme use and study follow-up, both groups will receive reminder texts (intervention fortnightly with additional email reminder; control monthly) during the intervention period of 12 weeks, then both groups will receive monthly reminder texts, including the approximate date for their next survey, until the 6-month follow-up. Intervention participants will have access to P2S for the 12 weeks. After 11 weeks, intervention participants will receive an email notifying them that their access to the P2S programme will expire within a week. Survival checks will be completed with AuSCR or HSRVR prior to telephone contact. All participants will be asked to complete a 6-month follow-up CATI. Participants will be reimbursed with an AU$50 gift card after the completion of the 6-month survey.

**Fig. 2 Fig2:**
[figure not shown]
Assessment schedule of enrolment, interventions, and assessments for participants

### Intervention

Participants randomised to receive the intervention will be sent an email and letter containing a link to P2S and their log-in details. The P2S programme is a modularised, tailored programme designed for individuals who have had a stroke to improve their HRQoL which may reduce their risk of a second stroke event. The P2S programme and its development is described in detail elsewhere [28]. Briefly, individuals are first presented with a loading module where they are asked questions to determine what information might be most relevant to the user. After completing the loading module, users are able to access the other seven modules (one module for each of the four health behaviours (Smoking, Alcohol Use, Diet, Physical Activity), one for Blood Pressure, one for Moods and Feeling, and the My Progress module (for participants to track their progress towards achieving goals).

During their 12-week access, intervention participants will be able to revisit sections of the programme as required, setting new goals, and recording progress throughout this time. Fortnightly text message and email reminders will be sent to prompt programme usage. Individuals will also receive a toll-free number that allows calls to the project team if they require assistance. Participants will be encouraged to use the online programme at least once a week and more often if they choose. Navigation through the programme will be flexible, with participants able to navigate around the programme freely, focussing on content areas of greatest interest or need.

### Minimal ethical care (control) group

Participants randomised to the control group will receive usual stroke follow-up care and will be sent an email and letter with links to Internet addresses of readily available, generic online health programmes designed for the general population (The Australian Department of Health ‘Quit Now’, ‘Australia’s Physical Activity and Sedentary Behaviour Guidelines’ and ‘Eat for Health’ sites; The National Health and Medical Research Council’s ‘Australian Guidelines to Reduce Health Risks from Drinking’; and the ‘MOODGym’ site). The use of an active control condition was chosen as it balances exposure to online health programmes and minimises the likelihood of changes in the treatment group due to non-specific therapeutic factors. P2S, which will only be accessible by entering user identification during the trial, will not be available to control group participants.

### Primary outcome measures

The primary outcome measure will be HRQoL, measured using the EuroQol 5 Dimensions, 5 Levels (EQ-5D-5 L) questionnaire [29], at 6 months. The EQ-5D-5 L consists of two stages of questions. Stage 1 contains five questions in the domains of mobility, self-care, usual activities, pain/discomfort, and mood (the EQ-5D). Each dimension has five levels: no problems, slight problems, moderate problems, severe problems, and extreme problems. The second stage adapts the EuroQol Visual Analogue Scale (EQ VAS), and asks respondents to numerically rate global health status from 0 to 100, and can be administered verbally [30, 31]. The justification for the EQ-5D-5 L is that it: (1) is very short and simple, taking 2–3 min and can be administered as a telephone interview; (2) is responsive to change in patients who have had a stroke; (3) is composed of multi-item scales and single items to examine differential effects; (4) has been used in, and is recommended for, stroke trials [32]; and (5) the construct, concurrent and discriminant validity, reliability, and acceptability (based on response rates and missing data) of the instrument with stroke patients has been well established [33].

### Secondary outcome measures

#### Cost-effectiveness

The main reportable outcomes for the cost-effectiveness analysis of the intervention will be (1) an average cost-effectiveness ratio, and (2) an incremental cost-effectiveness ratio, per Quality-adjusted Life Year (QALY). A modified version of the Client Service Receipt Inventory (CSRI) will be used in conjunction with the MBS and PBS data to determine use of health services (frequency, length and cost of physician consultations; allied health care; inpatient stays; outpatient episodes; medication use) and potentially other economic impacts (such as time off work due to disability) [34].

#### Smoking status

At baseline, a standard and previously validated item will assess smoking status ‘*Do you currently smoke any tobacco products?*’ (Daily, At least once a week, Less often than once a week, Not at all) [35]. At follow-up, 7-day point-prevalence abstinence (PPA) will be used to assess quit success using recommended items to determine the proportion of participants who have not smoked any tobacco in the preceding 7 days ‘*Have you smoked at least part of a cigarette in the last 7 days?*’ Seven-day PPA has high concurrent validity and reliability [36].

#### Alcohol consumption

The brief Alcohol Use Disorders Identification Test – Consumption (AUDIT-C), [37] will be used. The AUDIT-C is a three-item version of the more extensive AUDIT and has been found to be a valid and reliable screening tool for heavy drinking and alcohol abuse or dependence. Scoring for the AUDIT-C ranges from 0 to 12 with cut-offs of 3 for women (sensitivity 66–73%, specificity 91–94) [38, 39] and 4 for men are used to indicate heavy drinking (sensitivity 86%, specificity 72–89%) [39].

#### Fruit and vegetable intake

The Australian Recommended Food Score (ARFS) [40] will be used to assess fruit and vegetable consumption, a measure which has been validated in adults. The ARFS is strongly correlated with food frequency questionnaire nutrient intakes (fibre, vitamin A, beta-carotene, vitamin C, and minerals). To determine salt intake, participants will be asked ‘How often do you add salt to your cooking?’ and ‘How often do you use salt at the table?’ (Never/rarely, Sometimes, Usually, Always) [41].

#### Physical activity

Physical activity will be measured using the Godin Leisure Time Exercise Questionnaire (GLTEQ), [42] which measures the number of occurrences in a week in which a participant engages in periods of mild, moderate or vigorous exercise for 10 min or longer. Weights are then applied to the number of weekly occurrences of each type of exercise (mild, moderate, vigorous) and summed to calculate the number of metabolic equivalent or MET-minutes of exercise per week; it has acceptable reliability and validity.

#### Depression and anxiety

Depression and anxiety levels will be assessed using The Patient Health Questionnaire four-item (PHQ-4) [43]. The PHQ-4 is a validated and ultra-brief screening measure for both anxiety and depression. Scores range from 0 to 12, with categories of psychological distress being: none (0–2); mild (3–5); moderate (6–8); and severe (9–12). Subscale categories for anxiety and depression both range from 0 to 6 with a score of 3 or more considered positive.

#### Physical functioning and independent living

Physical functioning and independent living will be measured using the Barthel Index (BI) [44, 45] and Instrumental Activities of Daily Living (IADL) scales [46]. The BI measures activities of daily life on a 10-point scale related to self-care and mobility. The IADL questions attempt to capture the ability to live independently in the community.

#### Other secondary outcome measures

Other measures include hospital admission for recurrent stroke, myocardial infarction and all other causes, and data from medical health records. These data will be collected from national health care databases and will be used to inform resource-use assumptions in the cost-effectiveness analysis for patients utilising hospitals in health districts without access to an equivalent intervention.

### Additional measures

Patient and disease characteristics including age, gender, postcode, indigenous status, country of birth, hospital, type of stroke, whether the patient was able to walk independently on admission, and whether the patient was treated in a stroke care unit will also be collected. Adherence to the intervention, carer involvement, blood pressure awareness, and use of secondary prevention strategies will also be collected at 6 months. Programme usage data (i.e. timing and usage) will be collected as part of backend analytics from the web-platform hosting the P2S programme.

### Blinding

All baseline and follow-up telephone assessments will be conducted by independent health survey contractors blinded to experimental condition. Due to the nature of the interventions, blinding participant allocation and participants will be notified of the condition to which they have been assigned.

### Data collection

A commercial research company will be commissioned to collect baseline and follow-up data by CATI survey. MBS and PBS health data will be extracted from the national database at baseline and 6 months with the assistance of Department of Human Services, Canberra.

Study participant information and consent forms will have a unique study identification (ID) number. After formal enrolment into the trial participants will be assigned that unique study ID, allowing data to be stored in a re-identifiable format. The ID number will be used to identify participant data sets for comparison (i.e. baseline and follow-up surveys). Participant identifying details (i.e. names and contact details collected to enable follow-up) will be stored separate to other data, while the ID number will be attached to both.

### Statistical analysis

#### Primary analysis

Will be conducted according to the intention-to-treat (ITT) principle, comparing the change in HRQoL between groups from baseline to 6-month follow-up. The comparison will be done using a linear regression model, where the outcome variable will be the EQ-5D-5 L HRQoL score, and the main predictors of interest will be the baseline value of the outcome variable, and treatment group. The two stratifying variables, state of residence within Australia and stroke type at baseline, will be included in the model as covariates. The primary method of dealing with missing data will be through multiple imputation, this will provide a sensitivity analysis exploring how robust the results are when considering missing values. The missing data will be explored to test the underlying assumptions of multiple imputations. Adjusting for potentially imbalances in important prognostic variables and pattern mixture models will be used to correct for violations in the missing at random assumption.

#### Secondary analysis

Generalised linear mixed models will be used to examine between-group differences in changes in secondary outcomes between baseline and follow-up; appropriate distributional families and link functions will be used according to outcome type. The models will include fixed effects for time, group and the interaction between time and group, as well as stratification variables. Random subject-level intercepts will be included to account for serial correlations. Associations between programme usage and outcome will be examined where greater adherence to the programme will be expected to be associated with improved outcomes.

#### Cost-effectiveness analysis

In this study, a cost-utility analysis will be undertaken from the perspective of health care providers to identify whether the resources consumed to achieve the outcomes represent a cost-effective improvement over usual stroke follow-up care. The analysis will adhere to guidelines for conducting and reporting health economic evaluations [47, 48]. Given that the majority of resource savings are anticipated to arise following conclusion of the intervention, a patient lifetime time-horizon will be modelled founded on the trial outcomes. The primary measure of effectiveness for the economic evaluation will comprise HRQoL, as measured by EQ-5D-5 L, from which QALYs will be calculated using Australian utility weights. Resource utilisation for the respective trial arms will include: intervention development costs, health care costs derived from the AuSCR hospital *International Classification of Disease* (*ICD*) data, the CSRI data, and the MBS/PBS data. The *ICD* data will be translated to an estimate for cost differences between arms using allocations to diagnostic-related groups and according cost weights. It is implicitly assumed that differences between trial arms for non-stroke utilisation of inpatient services will be random. This assumption will be tested with the CSRI inpatient data and admitted patient data from a subset of health districts. Analysis of the QALYs and resource-use estimates will derive average and incremental cost-effectiveness ratios. Appropriate sensitivity and uncertainty analysis will be conducted.

A full statistical analysis plan will be written prior to analysis.

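### The economic analysis assumes no systematic effect on non-stroke inpatient use, which the trial itself sets out to estimate, and the planned check cannot establish that assumption

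*Protocol article*

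**What the plan says.** The Cost-effectiveness analysis section announces that "a cost-utility analysis will be undertaken from the perspective of health care providers", over a modelled patient lifetime. Its resource inputs by arm are development costs, hospital ICD data from the stroke registry, the CSRI data, and the Medicare and pharmaceutical claims data. After describing how ICD data become a cost difference through diagnostic groups, it adds: "It is implicitly assumed that differences between trial arms for non-stroke utilisation of inpatient services will be random". The safeguard follows directly: "This assumption will be tested with the CSRI inpatient data and admitted patient data from a subset of health districts".

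Other parts of the article bear on this:

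- Aims lists the effect of the programme on admission for recurrent stroke, myocardial infarction and all other causes as a secondary aim. Other secondary outcome measures repeats it: "Other measures include hospital admission for recurrent stroke, myocardial infarction and all other causes, and data from medical health records".
- The same section says of the admissions data: "These data will be collected from national health care databases and will be used to inform resource-use assumptions in the cost-effectiveness analysis". The sentence then ties that use to patients in health districts lacking an equivalent intervention.
- Cost-effectiveness, under Secondary outcome measures, says the CSRI together with the claims data will capture "frequency, length and cost of physician consultations; allied health care; inpatient stays; outpatient episodes; medication use". Inpatient stays are not restricted to stroke.
- Intervention describes modules on smoking, alcohol, diet, physical activity, blood pressure and mood.

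**The concern.** In a randomised trial, saying that a between-arm difference is random amounts to saying that treatment has no effect on it. So the economic section assumes an answer to a question that the Aims leave open. The assumption is not an obviously safe one, because the programme targets vascular risk factors and mood, which could plausibly bear on cardiac and other admissions.

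The perspective is that of health care providers, who pay for a cardiac or other admission as they do for a stroke admission. If non-stroke stays were not costed by arm, incremental cost would omit any real saving or excess there. The economic result could then sit awkwardly beside the trial's own estimate for all-cause admission. The direction of any such error is unknown.

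The text does not settle whether this happens. The CSRI is both a cost input and the instrument for testing an assumption that would hardly be needed if every stay were already costed by arm.

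**Working it through.** **1. The plan's own figure.** The only powered comparison is health-related quality of life (Sample size): 6 points, SD 24, correlation 0.6, 80% power, 5% significance (taken as two-sided).

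- Residual SD = 24 × √(1 − 0.6²) = 19.2.
- n per arm = 2 × [(1.96 + 0.842) × 19.2 / 6]² ≈ 160.7, that is 161, against 160 stated. Power at 160 is 79.8%.

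The figure reproduces. It says nothing about admissions, for which no power is stated.

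**2. Inputs for the check.**

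- From the protocol: 160 per arm at follow-up; 530 randomised 1:1, so 265 per arm; 40% completion as written, so 530 × 0.40 / 2 = 106 per arm.
- Assumed, because the protocol gives none: control proportions with any non-stroke admission by 6 months of 5%, 10%, 20% and 30%; true relative reductions of 20%, 30% and 50%; a district subset of 80 per arm (half of 160) or 53 per arm (one fifth of 265).

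**3. Formula.** Two proportions, two-sided 5%, counting rejections in the correct direction only (so values just under 5% can occur):

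power = Φ{[d − 1.96 × √(2p̄(1 − p̄)/n)] / √([p₁(1 − p₁) + p₂(1 − p₂)]/n)}, with d = p₁ − p₂ and p̄ = (p₁ + p₂)/2.

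Example: n = 160, p₁ = 0.30, p₂ = 0.21. The two standard errors are 0.0487 and 0.0485. Power = Φ[(0.09 − 0.0955)/0.0485] = Φ(−0.114) = 45.5%.

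**4. Results.** Power (%) for a 20% / 30% / 50% relative reduction, by control rate:

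| n per arm | 5% | 10% | 20% | 30% |
|---|---|---|---|---|
| 265 | 8.0 / 13.5 / 32.8 | 12.4 / 23.5 / 58.9 | 22.3 / 45.2 / 89.9 | 34.3 / 66.2 / 98.6 |
| 160 | 6.3 / 9.8 / 21.6 | 9.1 / 15.9 / 39.6 | 15.1 / 29.7 / 70.9 | 22.6 / 45.5 / 89.9 |
| 106 | 5.4 / 7.8 / 15.8 | 7.3 / 11.9 / 28.1 | 11.4 / 21.2 / 53.2 | 16.4 / 32.3 / 74.7 |
| 80 | 4.9 / 6.8 / 12.9 | 6.4 / 10.0 / 22.3 | 9.6 / 17.0 / 42.4 | 13.4 / 25.5 / 62.4 |
| 53 | 4.3 / 5.7 / 9.9 | 5.5 / 8.0 / 16.2 | 7.7 / 12.7 / 30.0 | 10.3 / 18.4 / 45.5 |

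**5. Precision.** The approximate 95% half-width for the difference is 1.96 × √(2p(1 − p)/n). At 160 per arm it is 4.8 points at a 5% rate and 10.0 points at 30%. A 30% relative reduction at those rates is 1.5 and 9.0 points. An interval centred on zero would therefore still include an effect of that size.

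**6. Data sources side by side.** Other secondary outcome measures takes admissions from national sources. Cost-effectiveness analysis has admitted patient data for only some health districts. Both may be true of different data sets, but the article does not say so, and the coverage decides both the power of the check and what can be costed.

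**The case against.** A reader might infer that non-stroke costs will be dropped from incremental cost once a significance test comes out null. The documents do not say that. CSRI data are a listed input for both arms, the CSRI covers inpatient stays of any kind, and the admissions data are said to inform resource use. No significance test, threshold or consequence is stated. The assumption follows the step that turns registry ICD data into costs, so it may disclose only a limit of that one data stream. Nor does the text say that the assumption is carried into the lifetime model. All of this stands, and the point cannot be put as an exclusion of costs.

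It is also true that an aim to examine an effect does not assert one, that the assumption is disclosed, that sensitivity and uncertainty analyses are promised, and that the details of the test may properly sit in an analysis plan not shown here.

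The admission rates and subset size are assumptions, and any admission (yes or no) is only a stand-in for the stays or costs that an economist would compare. Records obtained outside the telephone survey need not be limited to completers. But even with all 265 per arm, power for a 20% to 30% reduction does not exceed 66%. The weakness of the check does not depend on one chosen pair of rates.

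**Conclusion.** The point holds as a conflict between a stated economic assumption and a stated trial aim, joined to an ambiguity about what is costed. It does not show that costs are omitted.

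The planned check cannot establish the assumption. Over assumed rates of 5% to 30% and relative reductions of 20% to 30%, power is about 6% to 46% at 160 per arm and about 4% to 26% at 53 to 80 per arm. Only reductions near 50% at rates of 20% to 30% would be found with fair reliability at 160 per arm (71% to 90%). If completion really is 40% of 530, the CSRI-based check has 5% to 32% power for the 20% to 30% reductions. A null result is thus the likely outcome whether or not a moderate effect exists.

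The weight is moderate: this is a secondary analysis, and the remedy uses data already planned.

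**What to change.** In the Cost-effectiveness analysis section, or in the analysis plan still to be written:

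- State that all-cause inpatient stays, including myocardial infarction, are costed by randomised arm in the cost-utility analysis whatever the check shows, using the CSRI and the admissions data named under Other secondary outcome measures. If the assumption is true, this adds noise but no bias; if it is false, the stroke-only figure is the biased one.
- Report stroke-only inpatient cost alongside as a sensitivity analysis.
- Give the between-arm difference in non-stroke inpatient use with its confidence interval, and say that a non-significant result will not be taken as support for the assumption.
- Reconcile the national sources in one section with the district subset in the other: which admissions data exist, for which participants, and for what use.

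The cost is some wording and a little more costing work on data already to be collected. There are two drawbacks. All-cause costs are noisier, so the interval for incremental cost widens. CSRI stays will be known only for participants who complete follow-up, so the missing data need handling and the routine records should be used where they reach further.
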